### **8.3 Description of the statistical methods foreseen and the planned intermediate assessments**

Non-parametric Wilcoxon signed rank test

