Due to the progressive nature of DMD MFM values and 2MWD decrease over time until free ambulation is lost (mean progression can be calculated based on data from the literature and correspond to predicted values (23, 24). In contrast, four of the five treated patients showed a marked improvement of their clinical and functional abilities. The mean total MFM (3,5%) and 2MWD (10 meter) improved. In addition, the MFM D1 subdomain (standing and transfers), which is the most informative dimension in ambulant DMD patients aged 6 years and over with a

mean decrease of 17.2% per year (23), improved by more than 6% in our treated DMD group. More importantly, this improvement is better than the maximal mean improvement reported for the total MFM and the D1 MFM subscore (both below 2%) after beginning a steroid treatment (standard symptomatic treatment of care)(25). Relevant changes observed in our trial are shown in table 2.

| Category    | Variable                  | mean  | median | SD   | range         | 95% CI         |
|-------------|---------------------------|-------|--------|------|---------------|----------------|
| calorimetry | REE, kcal/24 h            | -51.2 | -56.5  | 37   | -84 to -8     | -54 to -48.5   |
| calorimetry | carbohydrate oxidation, % | -17.9 | -11.3  | 18.4 | -44.8 to -4.4 | -20.7 to -15.1 |
| calorimetry | fatty acid oxidation, %   | 13.9  | 9.6    | 13.7 | 2.9 to 33.6   | 11.1 to 16.7   |
| Walking     | 2 min walking distance    | 9.58  | 9.6    | 29.3 | -40.3 to 30.6 | 6.8 to 12.4    |
| MFM         | total score, %            | 3.54  | 7.29   | 6.93 | -8.33 to 8.33 | 0.969 to 6.11  |
| MFM         | D1 subscore, %            | 6.15  | 7.69   | 11.6 | -12.8 to 15.4 | 3.58 to 8.72   |
| MFM         | D2 subscore, %            | 1.67  | 2.78   | 4.65 | -5.56 to 5.56 | -0.903 to 4.24 |
| MFM         | D3 subscore, %            | 1.91  | 0      | 5.43 | -4.76 to 9.53 | -0.665 to 4.48 |

Table 1: Descriptive statistics (mean, median, standard deviation, range, and 95% confidence interval) for selected variables of all five treated patients (change from baseline to post-treatment).

Individual and predicted (calculated using data from the literature (23,24)) MFM and the 2 min walking distance values of all treated patients are presented as follows:

[figure not shown]

Figure 2: Individual and predicted (calculated using data from the literature (23,24)) 2 min walking distance (A) and MFM (B) values of all treated patients.

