#### **4.3 Measure to minimise bias (randomising, blinding)**

Patients who meet the study admission criteria will be enrolled in the study and a single subject identification number will be assigned. Patients are allocated to the two study groups, L-citrulline and metformin or placebo, in a 1:1 ratio. The assigned number will be recorded in the CRF Visit 2. Drop outs after baseline visit (randomisation) will not be replaced.

The physiotherapists who perform the tests were trained and certified in Lyon where MFM has been established and validated.

This is a double blind, placebo controlled, randomized study.

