## **8. STATISTICS**

### **8.1 Definition of the primary end point and secondary endpoints**

- 1) Mean change of MFM D1 subscore from baseline to week 26 under L-citrulline/metformin therapy compared to placebo
- 2) Mean change of MFM total score, the D2, and D3 MFM subscores from baseline to week 26 under L-citrulline/metformin therapy compared to placebo

- 3) Mean change of walking distance from baseline to week 26 under L-citrulline/metformin therapy compared to placebo assessed with the six-minute walk test
- 4) Change of quantitative muscle MRI including muscle fat content (MFC) and T2 times of thigh muscles visualized by MRI (Magnetic Resonance Imaging) in both groups at week 26 versus baseline
- 5) Change in the plasma / urine concentration for markers of muscle necrosis (resting creatine kinase, plasma), oxidative stress (8OHdG, urine; carbonylated preteins, 4-HNE serum), nitrosative stress (nitrotyrosin, plasma; ADMA, serum; cGMP, urine), and change of miRNAs serum concentration in both groups at week 26 compared to baseline values and to values of age and sex matched healthy volunteers.
- 6) Mean change of quantitative muscle force (QMT) of knee extension and elbow flexion using hand held dynamometry (HHD) from baseline to week 26 under L-citrulline/metformin therapy compared to placebo

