## **8.2 Planned number of trial subjects with clearly stated justification (possibly power analysis)**

For sample size estimation the MFM D1 subscore was chosen. Baseline and post-treatment measurements of 5 patients are available from the pilot study. A semi-parametric approach for sample size estimation was chosen that made use of these data. For the 2 min. walking distance, a mean change from baseline to post-treatment of 10 m was expected (estimated from pilot data). For the MFM D1 subscore, a mean change from baseline to post-treatment of 6.1 % was expected (estimated from pilot data). Sample size estimation was repeated for a range of values smaller and larger than the expected mean changes. Further, the influence of two randomisation ratios for the verum/placebo groups, 1:1 and 2:1, on sample size was checked. Each sample size,  $n_i=1, \dots, 40 = 11, \dots, 50$  for the MFM D1 subscore, was evaluated by drawing 99 times an individual data set of size  $n_i$  from the pilot study data set (sampling with replacement). In each of these individual data sets, each patient was randomly assigned to a verum or a placebo group. For each patient, the post-treatment value was

Version 8, 10.09.2015

calculated as the sum of the baseline value and a random variate drawn from a normal distribution with mean and standard deviation estimated from the pilot data. In the case of the placebo group, the mean was set to  $-17.2/54 \times 16$  for the MFM D1 subscore (value taken from Table 2 in (39)). (The values from the literature refer to changes within one year, i.e. 54 weeks, and the pilot study lasted 16 weeks, thus the linear transformation of the values by  $/ 54 \times 16$ .) For the primary endpoint candidate (MFM D1 subscore), assuming a drop-out rate of 10 %, a randomisation ratio of 1:1, and a power of 0.8, c. 42 patients should be recruited in order to be able to analyse 38 complete datasets. Fig. 4 shows how the sample size behaves with regard to the MFM D1 subscore, the power, and the randomisation ratio.

[figure not shown]

Fig. 4. Sample size with regard to the MFM D1 subscore and the power for a randomisation ratio of 1:1. The numbers on the curves indicate the power. The arrow shows how to interpret the plot. The curves are smoothed and only serve illustrative purposes.

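### Section 8.3 names a paired within-group test (Wilcoxon signed rank), which contradicts the between-arm primary endpoint in 8.1 and the two-group simulation in 8.2; it is probably a misnamed rank-sum test

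*Protocol*

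**What the plan says.** Protocol section 8.3 consists of one line: "Non-parametric Wilcoxon signed rank test". No rank-sum, Mann-Whitney, t-test, analysis of covariance or other two-sample method is named anywhere in the protocol.

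The primary endpoint in 8.1 (also in 4.1 and 6.1) is "Mean change of MFM D1 subscore from baseline to week 26 under L-citrulline/metformin therapy compared to placebo". The design in 4.3 is parallel: "Patients are allocated to the two study groups, L-citrulline and metformin or placebo, in a 1:1 ratio". No crossover and no matching of verum to placebo patients is described.

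The simulation in 8.2 has the same two-group structure: "each patient was randomly assigned to a verum or a placebo group". Its verum input is "a mean change from baseline to post-treatment of 6.1 % was expected (estimated from pilot data", and the placebo group has its own mean, a literature decline scaled to 16 weeks. The result is 38 complete datasets, about 42 recruited, for "a randomisation ratio of 1:1, and a power of 0.8". Section 8.2 does not say which test was applied to the simulated data.

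**The concern.** A signed rank test asks whether paired differences are centred on zero. The only pairs in this trial are baseline and week 26 within a patient, so the test can ask only whether one arm changed. It cannot compare two independent arms.

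Zero change is also the wrong reference within an arm. Sections 3.1.1 and 4.1 expect an untreated D1 decline of 17.2% per year in ambulant patients aged 6 and over, and 4.1 states the aim as slowing the natural course. Under a within-arm test, natural decline alone yields significant results, and a drug that fully stops the decline yields a null one.

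This is not a detail left to a statistical analysis plan. A method is stated, and it does not fit the endpoint it serves. Without a correction, the valid test would be chosen outside the protocol.

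**Working it through.** **Inputs**

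- Verum change: +6.15 (pilot table in 3.1.1; 8.2 rounds to 6.1).
- Placebo change: −17.2/54 × 16 = −5.10 (8.2).
- SD of change: 11.6 (pilot table, five patients, 16 weeks), used for both arms.
- Complete datasets: 38 at 1:1, so 19 per arm (8.2).
- Alpha: 0.05 (8.4). Sidedness is not stated; two-sided is assumed.
- Changes are drawn from a normal distribution, as in 8.2. Simulated results use 20,000 trials per scenario.

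**Step 1: reproduce the plan's figure with a between-arm test**

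Difference = 6.15 − (−5.10) = 11.25. Standardised difference = 11.25/11.6 = 0.97.

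| Per arm | Rank-sum power | Two-sample t power |
|---|---|---|
| 17 | 0.755 | 0.783 |
| 18 | 0.781 | 0.807 |
| 19 | 0.803 | 0.828 |
| 20 | 0.827 | not computed |

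The smallest size at which rank-sum reaches 0.80 is 19 per arm, or 38 in total, which is the stated number. A t-test would need 18 per arm, or 36. The plan used only 99 draws per sample size, so the Monte Carlo standard error of its own power estimate is √(0.8 × 0.2/99) = 0.040. That is too coarse to tell the two tests apart.

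**Step 2: the test as named, on the same inputs**

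With 19 per arm, the signed rank test has power 0.58 in the verum arm (+6.15) and 0.42 in the placebo arm (−5.10). Neither figure is the stated 0.8, and neither is a comparison between arms.

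**Step 3: behaviour when the drug does nothing, and when it halts decline**

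The annual decline scaled to week 26 is 17.2 × 26/54 = 8.28 on the 54-week year used in 8.2, or 17.2 × 26/52 = 8.6 on a 52-week year. SD 11.6 is assumed to hold at week 26. If both arms have rejection rate p, the chance that exactly one is significant is 2p(1 − p):

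- p = 0.43: 2 × 0.43 × 0.57 = 0.49
- p = 0.82: 2 × 0.82 × 0.18 = 0.30
- p = 0.85: 2 × 0.85 × 0.15 = 0.26

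| True mean change, verum / placebo | Signed rank rejects | Exactly one arm significant | Rank-sum rejects |
|---|---|---|---|
| −5.1 / −5.1 (no effect) | about 43% of arms | about 49% | about 5% |
| −8.28 / −8.28 (no effect) | about 82% of arms | about 30% | about 5% |
| −8.6 / −8.6 (no effect) | about 85% of arms | about 26% | about 5% |
| 0 / −8.6 (decline fully halted) | about 5% in the verum arm | not used | about 57% |

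The rank-sum rate under no effect does not depend on the common decline, because both arms shift together.

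**The case against.** The strongest reply is that this is a slip in naming and not a flaw in design. The between-arm contrast is fixed in 4.1, 6.1 and 8.1, and the simulation in 8.2 is built on it. That reply stands. A reader might infer from 8.3 that the trial is designed to ignore its control group or wastes its randomisation. The documents do not support that: it follows only if 8.3 is applied literally against 8.1.

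A reader might also infer that the power calculation demonstrably used the rank-sum test. Section 8.2 names no test, and 99 draws per size cannot separate rank-sum from t. The inputs point to some between-arm test; which one is an inference.

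The protocol states no rule for declaring success when exactly one arm is significant, so those percentages illustrate a possible misuse and not a planned decision.

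Finally, the signed rank test is not out of place everywhere. Endpoints 4 (MRI) and 5 (laboratory markers) in 8.1 are worded partly as change from baseline within each group, and a paired test can answer that part. A reader might conclude that every secondary endpoint needs the between-arm test; as worded, only 2, 3 and 6 do.

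None of this removes the contradiction for the primary endpoint.

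**Conclusion.** Section 8.3 is wrong as written for the primary endpoint: the only method it names cannot test the contrast defined in 8.1 and simulated in 8.2. The likeliest explanation is that rank-sum was meant.

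Read literally, the error is large. With no drug effect, an arm is significant in roughly 43% to 85% of cases, depending on the common decline, where a between-arm test holds about 5%. With decline fully halted, the active arm is significant in only about 5%, where rank-sum has about 57% power.

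These sizes assume normal changes, two-sided testing and a common SD of 11.6 carried from a 16-week pilot of five patients to week 26. The contradiction itself needs none of these assumptions. The sample size is not called into question by this point.

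**What to change.** In 8.3, before unblinding, replace the signed rank test with the two-sample Wilcoxon rank-sum (Mann-Whitney) test of change in D1 from baseline to week 26, verum against placebo, reported with the Hodges-Lehmann difference and its 95% confidence interval. State that alpha is two-sided, if that is meant.

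Use the same contrast for secondary endpoints 2 (MFM total, D2, D3), 3 (six-minute walk) and 6 (muscle force). Keep the signed rank test only for the within-group parts of endpoints 4 and 5, and say so. A baseline-adjusted model of D1 is an optional addition and is not needed to resolve the contradiction.

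The cost is a few lines of protocol wording. No patients, visits or data are added, and the 38 complete datasets (about 42 recruited) stay as they are.

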### **8.4 Planned significance level**

$\alpha = 0.05$

### **8.5 Handling of missing data or of data in the case of subjects halting the trial prematurely**

Last observation carried forward

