### **Metformin**

For the planned study a dosing of 250 mg metformin, respectively placebo, three times a day (750 mg daily) will be given during 26 weeks. In our mentioned recent pilot study we used 2 x 250 mg/d metformin and observed a very good safety profile, no serious side effects, and no drop-outs. To increase the efficacy and facilitate the dosage regimen, we want to increase the metformin dose and provide it also at a three times daily dosage (750 mg daily). A dose up to 2000 mg/d seems to be associated with a low incidence of gastrointestinal side effects in children (7) thus a dose of 750 mg/d seems to be safe and might even more activate the muscle metabolism. At the beginning of the treatment with metformin nausea, vomiting, diarrhoea and abdominal pain may occur. Usually these symptoms decrease spontaneously after a few days. To ensure the blinding, metformin capsules produced by the hospital pharmacy of the University Hospital Basel will be used in this trial. They have to be stored at room temperature (15-25°C).

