## **4. DESIGN OF THE TRIAL**

### **4.1 Targeted primary endpoint and secondary endpoints**

#### Primary outcome measure

- 1) Mean change of MFM D1 subscore from baseline to week 26 under L-citrulline/metformin therapy compared to placebo

Several tests have been reported in the literature to assess muscle strength and functional ability, to monitor the progression of the disease, and to evaluate the results of drug interventions and rehabilitation. However, most instruments involve only ambulant patients, making adjustments and/or additional assessments necessary when the disease progresses. The MFM, a validated assessment tool to measure motor function in both ambulant and non-ambulant patients with neuromuscular disorders, was developed in 2005 in France. It includes 32 items that evaluate three dimensions of motor performance, including specific motor functions, such as transfers and standing posture (D1), proximal and axial (D2), distal (D3) and a total MFM score involving all of the motor dimensions. The items are scored and summed to comprise a total score, in which the maximum represents normal motor function. The instruction manual, validation examinations and other publications using the MFM can be downloaded at the MFM website (27). In a recent work in DMD, the annual decrease of the total score was 5.8% for the whole group of DMD patients, indicating an overall decline in motor capacities. However, examination of the D1, D2, and D3 subscores independently provided more information depending on the stage of the disease. Indeed, in ambulant patients with DMD, D1 was the most informative dimension, with a mean decrease of 17.2% per year before loss of ambulation in patients aged 6 years and over. After loss of ambulation, D2 became the most informative and showed an average decrease of 9.4% per year. In patients over 14 years, the average decrease in D3 was 10.8% per year (23). D1 seems to us to be particularly interesting because it is related to loss of ambulation and is responsive to short-term changes (3 months) and should provide sufficient information in a 6 months trial. Furthermore, in our own 16 week L-arginine and metformin pilot trial (see below 2.2.4) in ambulant DMD patients the D1 subscore showed the best effect size of all evaluated clinical parameters. Timed clinical functional assessments included the 2 min walking distance in meter (2MWD). In addition to the MFM timed clinical functional assessments (as the 6 min or 2 min walking distance in meter (6MWD /2MWD)) are helpful to assess the muscle function in children with DMD. Due to the progressive nature of DMD MFM values and 2MWD over time until free ambulation is lost (mean progression can be calculated based on data from the literature and correspond to predicted values) (24,25). The 6MWD is also a validated tool to measure the distance an individual is able to walk over a total of six minutes on a hard, flat surface. The goal for the individual is to walk as far as possible in six minutes. The individual is allowed to self-pace and rest as needed as they traverse back and forth along a marked walkway. Data from 112

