### **8.6 Definition of the evaluation groups**

Intention-to-treat (ITT) analysis

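### Last observation carried forward contradicts the protocol's own model of declining D1, and the resulting bias has a direction that the protocol cannot predict

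*Protocol*

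**What the plan says.** Section 8.5 consists of one line: "Last observation carried forward". Section 8.6 sets the analysis population: "Intention-to-treat (ITT) analysis". Section 4.3 adds that boys lost after randomisation are not replaced. Each of them therefore enters the primary comparison, "Mean change of MFM D1 subscore from baseline to week 26 under L-citrulline/metformin therapy compared to placebo", with a carried value.

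Section 4.1 describes D1 in ambulant patients "with a mean decrease of 17.2% per year before loss of ambulation in patients aged 6 years and over". Section 8.2 applies that decline to the placebo arm, linearly in time, and plans for 10% drop-out.

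MFM is scheduled at screening (used as baseline), week 13 and week 26. Section 9.2 also requires it at the final examination after premature withdrawal.

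**The concern.** The planning assumes steady decline, while the analysis assumes that a boy stops changing on the day he is last measured. Both cannot hold.

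What LOCF does to the treatment difference depends on how many boys leave each arm, when they leave, and how they would have fared afterwards. The primary result would then partly reflect the pattern of drop-out. Because a filled-in value is analysed as if measured, the standard error is also wrong.

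The protocol fixes this rule itself, so it is not a detail left to a statistical analysis plan.

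**Working it through.** **Inputs.** D1 decline is 17.2% a year (section 4.1), read as points on the D1 scale because section 8.2 adds it directly to baseline values. The SD of D1 change is 11.6 (pilot table, section 3.1.1, five boys). About 42 are recruited 1:1, so 21 per arm, with 10% drop-out (8.2). Alpha is 0.05 (8.4), taken as two-sided. The split of losses by arm is not given, so the splits below are assumptions.

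**The plan's own figure.** Section 8.2 states: "For the MFM D1 subscore, a mean change from baseline to post-treatment of 6.1 % was expected". The placebo change is −17.2/54 × 16 = −5.1, so the planned difference is 6.1 + 5.1 = 11.2. With SD 11.6 and 19 per arm, power is 0.825 (t-test) or 0.794 (simulated rank-sum). For drop-out, 38 × 1.1 = 41.8 and 38/0.9 = 42.2. The stated 38 analysed and about 42 recruited are reproduced.

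**Change that LOCF leaves out.**
- Only baseline available: 17.2 × 26/52 = 8.6 points.
- Last seen at week 13: 17.2 × 13/52 = 4.3 points.
- With the protocol's 54-week year: 8.3 and 4.1.

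**Bias in the difference, verum minus placebo.** Let p be the share lost in an arm and u the mean change that its drop-outs would have had after their last measurement. Then bias = −p(verum) × u(verum) + p(placebo) × u(placebo).

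If there is no treatment effect, u is negative and equal in both arms, and the bias favours the arm that loses more:

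| Losses | Baseline carried | Week 13 carried |
|---|---|---|
| 2 vs 2 | 0 | 0 |
| 3 vs 1 | 2/21 × 8.6 = 0.8 | 2/21 × 4.3 = 0.4 |
| 4 vs 0 | 4/21 × 8.6 = 1.6 | 4/21 × 4.3 = 0.8 |

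On the plan's own values (+6.1 and −5.1), with baseline carried:
- 4 verum losses, no placebo losses: bias = −4/21 × 6.1 = −1.2, and the difference falls from 11.2 to 10.0.
- 2 losses in each arm: 11.2 × 19/21 = 10.1.

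Both work against verum.

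**Type I error.** 20,000 null trials were simulated, 21 per arm, both arms falling 8.6 points, SD 11.6. Two-sample tests were used because the endpoint compares arms. Two-sided results:
- 4 vs 0, baseline carried: 7.0 to 7.2% (t-test), 7.6 to 7.8% (rank-sum).
- 4 vs 0, week 13 carried: 5.4 to 5.6% (t-test), 5.7% (rank-sum).
- 3 vs 1, baseline carried: 5.1% (t-test), 4.9% (rank-sum).
- 2 vs 2, baseline carried: 4.3% (t-test), 3.6% (rank-sum).

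The excess falls on one side. By rank-sum, false positives favouring the arm with more losses are 7.2% (4 vs 0) and 4.0% (3 vs 1) with baseline carried, against a nominal 2.5%. The 2 vs 2 result shows the standard-error fault alone: there is no bias, yet the test misses its nominal level because a carried baseline is a change of exactly zero.

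**The case against.** The strongest reply is section 9.2. A boy who withdraws has a final examination that includes MFM, so the carried value normally dates from withdrawal. Carrying baseline for the full 26 weeks needs a very early exit or a missed final visit. This stands, and it makes the baseline-carried figures an upper bound. It does not remove the bias, because change from withdrawal to week 26 is still set to zero.

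The second reply is size, and it also stands. The worst case above, 1.6 points, is about 15% of the planned 11.2 (1.64/11.2) and less than half a standard error (11.6 × √(2/21) = 3.6). If each loss is equally likely in either arm, all four fall on verum with probability 1/16.

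A reader might infer that LOCF will favour verum, because section 2.2 warns: "At the beginning of the treatment with metformin nausea, vomiting, diarrhoea and abdominal pain may occur". The protocol does not support that prediction. The next sentence there says that these symptoms usually settle within days, and the pilot had no drop-outs, though in only five boys and at a lower metformin dose. Placebo boys who worsen could equally leave. Nor is every drop-out spared decline: pilot D1 changes ran from −12.8 to +15.4, so the argument holds only on average.

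A reader might also extend the point to the six-minute walk, supposing that a boy who loses ambulation keeps his last distance. The protocol does not say so. Loss of ambulation is not among the stopping conditions in section 4.2.2, and the decline cited after age 7 is 12 m a year, about 6 m over 26 weeks.

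**Conclusion.** The concern holds as a fault in the rule: LOCF contradicts the disease model that the protocol uses for planning, biases the week-26 difference when losses or trajectories differ by arm, and misstates the standard error. With no true effect and all of the planned losses in one arm, the bias is 0.8 to 1.6 points, and two-sided type I error is about 5.5% to 7% by t-test (just under 8% at most by rank-sum). With a 3 versus 1 split it stays near 5%. If verum works as planned, the bias runs the other way.

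These figures assume linear decline at the cited rate, the pilot SD of 11.6 from five boys, 21 per arm and the stated splits. The effect would matter more if losses were heavier or more lopsided, or if the true benefit were well below 11.2 points.

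Error rates of 11% to 22% can be produced, but only with every loss on verum and baseline carried, plus six losses instead of about four, an assumed SD near 6, or both. The documents do not support them as a headline. This is something to correct before unblinding, not a fatal flaw.

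**What to change.** Replace section 8.5 with one of two primary rules:
- a likelihood-based repeated-measures model on D1 at weeks 13 and 26, with arm, visit, arm-by-visit and baseline D1, and the week-26 contrast as the primary comparison; or
- multiple imputation of week-26 D1 that uses the week-13 and withdrawal-visit values.

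State how withdrawal-visit measurements enter, and how a boy with no D1 value after baseline is handled, so that the analysis remains intention-to-treat. Add a reference-based sensitivity analysis in which drop-outs follow the placebo trajectory. Keep LOCF at most as a further sensitivity analysis.

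The cost is a change of wording before unblinding and some extra analysis work. No visit, measurement or patient is added, because the MFM assessments are already scheduled. The downside is reliance on model assumptions in a trial of about 42 boys.
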